## Abstract

**Introduction:**

Similar to chronic pain conditions, individuals with endometriosis can be affected by central sensitization syndrome (CSS), which is characterized by a loss of analgesia and central amplification of pain. Transcranial direct current stimulation (tDCS) has shown potential as an effective intervention to improve pain generated by other chronic pain conditions impacted by CSS, such as fibromyalgia and chronic pelvic issues. This study aims to evaluate the effectiveness of tDCS on pain, fatigue, and quality of life among patients affected by endometriosis.

**Methods:**

This is a single-center, parallel, double-blinded, randomized, controlled clinical trial protocol study. We aim to recruit 40 participants affected by endometriosis (active group, n = 20; sham group, n = 20). Anodal tDCS will be delivered at an intensity of 2mA, applied over the primary motor cortex for 20 minutes per day for 10 consecutive days. There will be four assessment times: 1 week before beginning the intervention; on the 10^th^ day following the last tDCS session; and 1 and 2 months after the last tDCS session. Pain evaluated by the algometry will be the primary outcome. Pain intensity, quality of life, fatigue, and global perception of change will be the secondary outcomes. We will calculate the effects of the active versus sham stimulation on primary and secondary outcomes by using generalized estimated equations or mixed model analysis. The effect size calculation will represent the effect measure. We expect that only the active group show reductions in pain, fatigue, and quality of life. The results of this trial will produce an important first step in providing evidence on the effectiveness of neuromodulation for the management of pain and will provide data to support new studies on tDCS.

**Registration:**

Brazilian Clinical Trials Registry (RBR-4q69573).

## Introduction

Endometriosis is a recurring condition affecting 6%–10% of women during childbearing age [1]. Approximately 35%–50% of women affected by endometriosis regularly experience painful symptoms in the pelvic region [1]. The chronic, benign, inflammatory, and estrogen-dependent lesions inside or outside the peritoneal cavity characterize the endometriosis [2]. The main symptoms presented by the women are related to chronic pelvic pain, dyspareunia, dysuria, dyschezia, and irregular uterine bleeding [3]. In this sense, endometriosis has been considered a debilitating condition due to its significant impact on physical, sexual, reproductive function, sleep quality, fatigue, and quality of life [3, 4].

There is evidence showing that the chronic pelvic pain experienced by women may generate changes in pain processing involving both neural input and output [5]. The altered central adaptation or central sensitization syndrome is associated with heightened pain sensitivity, including hyperalgesia, allodynia, expanded receptive fields, prolonged electrophysiological discharge, and persistent unpleasant sensations after painful stimuli [6–8]. It is important to highlight that central sensitization syndrome does not necessarily lead to hypersensitivity to pain [9].

Therapies that directly modulate brain activity in specific neural networks may effectively alleviate chronic pain associated with central sensitization syndrome [5]. Among various central neurostimulation methods, transcranial direct current stimulation (tDCS) has recently emerged as a non-invasive, painless, and safe modality [5]. tDCS has the capability to alter cell membrane potential and cortical excitability [10], influencing the resting potential of neuronal membranes and facilitating depolarization and hyperpolarization [11]. Consequently, the current flow appears to enhance excitability in motor areas while suppressing deeper brain regions, such as the cingulate, amygdala, and accumbens, which are associated with pain perception and control [10].

Clinical trials have demonstrated the efficacy of tDCS as an intervention for chronic pain, including cases of refractory pelvic pain and primary dysmenorrhea. The authors described significant improvements in pain perception and emotional aspects of pain [5, 12–14]. These studies consistently reported a low incidence of adverse effects associated with tDCS application, describing side effects as mild and transient, including itching, tingling, headache, burning sensation, and discomfort [12–15]. However, a scoping review [16] suggested that further investigations are warranted, emphasizing the need for studies with larger sample sizes.

Despite the positive impact of tDCS on several chronic pain conditions, function, and mood [15–17] to date, only one trial reported the use of tDCS in endometriosis [18]. The authors observed an increase in the pressure pain threshold sustained for one week after the end of the treatment [18]. However, as endometriosis is a complex condition that impacts not only pain but also fatigue and quality of life, higher-level evidence mirroring clinical practice focused on women’s health to evaluate the effectiveness of the technique is needed. Also, the use of tDCS on specific brain regions may lead us to a deeper understanding of central nervous system dysfunction and recovery. Therefore, this innovative protocol holds the potential to revolutionize the endometriosis treatment involving an intervention in the central nervous system.

Considering these assumptions, this protocol randomized-controlled trial aims to investigate the effectiveness of a standardized 10-session tDCS compared to sham tDCS for pain in patients affected by endometriosis. The secondary objectives will determine the impact of tDCS on fatigue and quality of life in patients affected by endometriosis.

## Methods

### Study design and setting

This single-center, parallel, randomized, double-blinded protocol clinical trial will follow the Guidelines for Standard Protocol Items: Recommendations for Interventional Trials. This study was registered in the Brazilian Clinical Trials Registry prior to initiation (ID: RBR-4q69573). The Woman Health Lab of the Federal University of Rio Grande do Norte will store the data and after five years the principal investigator will discharge them.

For stimulation, 30 seconds of gradual current ramp-up and ramp-down will be performed. Subsequent tDCS sessions will be identical and will always take place at the same time of day as the initial application. The sham tDCS intervention will follow the same protocol. However, after a gradual 30-second current ramp-up to initiate the current delivery, the stimulator will be switched off during the 20-minute protocol. These methods generate the same initial sensory sensations as the active tDCS, such as itching and tingling sensations on the scalp during the first few seconds of electrostimulation [17, 23]. Fig 1 illustrates the participants’ timeline during the study (SPIRIT Schedule).

**Fig 1 pone.0306405.g001:**
[figure not shown]
Spirit schedule. **Note:** EHP-30: Endometriosis Health Profile Questionnaire. Facit-F: Functional Assessment of Chronic Illness Therapy Fatigue Scale. PGI: Patient Global Impression.

### Outcomes

The primary outcome will be patient-reported pain using the sensitivity to ventral pressure by the algometry. Pressure pain threshold and tolerance will be measured (in kg/cm^2^) by a pressure algometer (MedDor, Minas Gerais, Brazil) positioned perpendicular to the skin and applied by the same trained evaluator. The examiner will place the rubber tip (1cm^2^) over the examination area and gradually increase the pressure by approximately 1 kg/s [24]. The pain threshold will record when the patient first reports the beginning of pain perception through the phrase “It started”. For pain tolerance, the participant will sustain the maximum pressure of the algometer until reporting an inability to tolerate the pressure through the phrase “Stop” [25]. Participants must repeat exactly these two sentences for complete standardization of the exam. We will register the pain threshold and tolerance in the moment the individual starts feeling pain and does not support the pain anymore, respectively. For the perception of pain intensity, a painful mechanical stimulus will last 5 seconds through the mid-point between the pressure pain threshold and the pressure pain tolerance previously obtained from each participant. Algometry will be performed laterally on the anterosuperior and anteroposterior iliac spines (Fig 2). We will sum the results of the ventral measurement of the right and left sides to calculate the mean of the results. The calculation will be the same for dorsal [26]. It is important to note that algometry demonstrates validity and internal consistency among evaluators ranging from 0.84 to 0.99. Correlations varied from very strong (r = 0.73–0.74) to nearly perfect (r = 0.99). Inter-rater reliability yielded moderate results (r = 0.55–0.60; Cronbach’s α = 0.71–0.75) [24]. Secondary outcomes will include the assessment of pain through the visual analogue scale, Brief Pain Inventory (BPI), quality of life (30-Item Endometriosis Health Profile [EHP-30]), fatigue (Functional Assessment of Chronic Illness Therapy–Fatigue [Facit-F]), and Patient Global Impression of Change [PGI-C] induced by the intervention. Moreover, adherence (number of missed sessions), attrition, and adverse events (headache during or within 6 hours after tDCS sessions, dizziness during or within 6 hours after tDCS sessions, intolerance to electrical stimulation treatment, and any other adverse events that participants attribute to the tDCS that have not previously been reported will be recorded.

**Fig 2 pone.0306405.g002:**
[figure not shown]
Test sites for pressure pain sensitivity testing. Red crosses indicate the local algometry in the ventral (A) and dorsal (B) regions.

For pain assessment, we will use the visual analogue scale that presents a strong reliability for assessing chronic pelvic pain, with an intraclass correlation coefficient of 0.99 [27]. The visual analogue scale is a one-dimensional measure of pain intensity that consists of a continuous scale composed of a horizontal line, 10 centimeters (100 mm) long, anchored by two verbal descriptors, one for each extreme symptom [28]. The scale is anchored by “no pain” (score of 0) and “worst imaginable pain” (score of 100 [100 mm scale]). Participants will be asked about the worst pain on the day of assessment and will then self-complete the visual analogue scale. They will indicate on a vertical line the point that represents the intensity of their pain [28]. The visual analogue scale is the pain index frequently used by subjects with pelvic pain [29]. The BPI questionnaire is validated for the Brazilian population and assesses the intensity (domain 1) and interference of pain (domain 2) in general activities, mood, walking ability, normal work, relationships with others, sleep, and enjoyment of life. The BPI shows an intraclass correlation coefficient ICC of 0.62 for the intensity subscale, with a minimal detectable change of 2.57. For the interference subscales, the intraclass correlation coefficient is 0.76, with a minimal detectable change of 2.34 [30]. The BPI presents an 11-point scale ranging from 0 (no pain/no interference) to 10 (as bad as it can be) [31]. In addition, BPI includes a corporal diagram to assess pain location (item 2), measures the percentage of pain relief (item 8), and requests patients to describe which treatments are performed to control pain. The scores for the two dimensions range from 0 to 10 and are calculated using the mean of the total items. Higher scores represent higher pain intensity and pain interference [32].

The EHP-30 is valid, stable, and specific quality of life measure for women diagnosed with endometriosis. According to the Bland-Altman plots, the EHP-30 presents excellent test-retest reliability for measure quality of life in women with endometriosis [33]. It is a 30-item questionnaire that assesses in five dimensions: pain, control and helplessness, emotional well-being, social support, and self-image, and a modular questionnaire with 23 items distributed in six scales: sexual relationships, work, the medical profession, infertility, relationships with children, and treatment. Each dimension is evaluated in a score from 0 to 100, the result is inversely proportional to the quality of life [34].

The Facit-F scale evaluates physical fatigue, functional fatigue, emotional fatigue, and social consequences of fatigue. The Facit-F scale presents an excellent internal consistency measured by Cronbach’s coefficient α ≥ 0.88, and demonstrates an intraclass correlation coefficient ≥ 0.75 [35]. It contains 13 items with five responses ranging from “none” to “very much.” Items are scored from 0 to 4, added, multiplied by 13, and divided by the number of items actually answered. The global score ranges from 0 to 52, and higher scores reflect less fatigue [36].

The PGI-C will measure change perception. PGI-C is a simple evaluation method composed of a 7-item scale, ranging from 1 (no change) to 7 (much ​​better), in which the patient evaluates the extent to which the intervention positively impacted their condition. This scale can identify minimal clinically important changes, which are sometimes not noticed in pain questionnaires or physical examinations [37]. Madani et al. showed that the PGI-C presents a coefficient sensitivity to change of 0.85 [38].

**Fig 3 pone.0306405.g003:**
[figure not shown]
Protocol flow chart. **Note:** BPI: Brief Pain Inventory; EHP-30: Endometriosis Health Profile Questionnaire; Facit-F: Functional Assessment of Chronic Illness Therapy–Fatigue Scale; PGI-C: Patient Global Impression of Change.

### Sample size

The estimated sample size required for this study is based on a previous study for chronic pain [40]. The calculator is freely available at https://glimmpse.samplesizeshop.org. To determine the sample size, we employed the Hotelling Lawley Trace statistical test with a power of 0.8 and an alpha error of 0.05 for pain assessment using the visual analogue scale. We accounted for two repeated measure dimensions, with the fixed predictor divided into two groups (active and sham), considering effects for group, time, and the interaction between group and time. The expected mean values per group for pain were 6.12 and 3.06 for the active group and 4.93 and 4.37 for the sham group, with a standard deviation of 3. Assuming constant variability across time (sphericity being 1), this analysis resulted in a total sample size of 94 participants. To account for anticipated attrition, we plan to recruit an additional ten participants, totaling 104 participants (active group, n = 52; sham group, n = 52).

### Statistical analysis

Statistical analyses will be performed using SPSS software version 21.0 (IBM Corp., Armonk, NY, USA). All tabulated data will be analyzed by a blinded researcher through a sequence of randomized codes generated for data analysis. Clinical and sociodemographic characteristics will be described by means and standard deviations for continuous parameters and by frequency for dichotomous variables. By the end of the data collection, the blinded researcher and the researchers who evaluated the patients will check for double data entry and any other problem related to the data tabulation. The t-test and Qui-square test will analyze the continuous and dichotomous data for sociodemographic characteristics, respectively. The generalized estimating equations (GEE) or generalized mixed models will analyze the clinical data (primary and secondary outcomes: algometry, visual analogue scale, EHP-30, Facit-F) at baseline, final assessment (after 10 days of intervention), and follow-ups. According to the data analysis (residuals Q-Q plot, and histogram), we will choose the best distribution to represent the data. Also, we will decide to insert fixed or random factors to the constant based on A/C, B/C, and Q/C indexes, Chi-Square/DF, and the intraclass correlation coefficient. The link function will estimate the results according to the distribution of the dependent variable. Time, group (active and sham groups), and the interaction between them will represent the independent factors. The mean, mean difference, standard deviation, confidence interval, and p-value for baseline, final assessment, and follow-ups, will represent the data. It is important to mention that the PGI-C and sub-items from the BPI will be analyzed as continuous or dichotomic variables using regression analysis (linear or logistic) to explore the predictors of pain intensity and interference. The analysis will be conducted using generalized mixed models or Generalized Linear Mixed Models. We aim to verify the interaction between time and group, adjusting for confounders and modifiers effects if necessary. Also, the Wald x^2^ test will assess the significance of individual independent variables in the model. In contrast, the Bonferroni test will compare subgroups of independent variables [42]. Intention-to-treat analysis of missing data will be analyzed through follow-up data from those who do not complete the treatment protocol. If needed, we will perform imputation followed by sensitivity analysis, using the last value carried forward or group means. In the intention-to-treat analysis, we will select the most conservative value to avoid overestimating the results and confounding the analysis. For the sensitivity analysis, we will test the robustness of our results by analyzing all imputed datasets and describing any differences in the outcomes compared to the original analysis using generalized mixed models or generalized linear mixed models. If necessary, we may utilize the type III regression when dealing with unequal sample sizes and unbalanced designs that involve interactions between variables or missing data. This approach enables us to assess the unique contribution of each variable to the model’s prediction. Moreover, we will analyze and describe potential outliers based on the model’s residual plots. Additionally, sensitivity analyses may be performed to assess differences with and without the outliers. Effect sizes for interactions will be calculated for all outcomes using the partial η^2^ and mean difference. The significance level will be defined in all statistical testing as a p-value less than 0.05.

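### The primary model treats baseline as a response, which gives up precision, and it leaves model choice and small-sample inference unfixed

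*Protocol article*

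**What the plan says.** All of this is in the Statistical analysis section of the protocol article.

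- **Model family:** "The generalized estimating equations (GEE) or generalized mixed models will analyze the clinical data". No rule is given for choosing between the two.
- **Times modelled:** the outcomes enter "at baseline, final assessment (after 10 days of intervention), and follow-ups". Participant timeline gives two follow-ups, so there are four times and the group-by-time interaction has 3 df.
- **Factors:** "Time, group (active and sham groups), and the interaction between them will represent the independent factors". No baseline covariate is named, and nothing constrains the arms to a common baseline mean.
- **Distribution:** "According to the data analysis (residuals Q-Q plot, and histogram), we will choose the best distribution to represent the data". The link follows from that choice.
- **Effects:** "we will decide to insert fixed or random factors to the constant based on A/C, B/C, and Q/C indexes", together with a chi-square/DF ratio and the intraclass correlation.
- **Inference:** a Wald chi-square test at 0.05, with no small-sample correction mentioned.
- **Effect measure:** "Effect sizes for interactions will be calculated for all outcomes", using both partial eta-squared and the mean difference. Confidence intervals are also planned.
- **Safeguard:** the analyst is blinded and works on coded groups.

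**The concern.** There are two separate issues.

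**Precision.** When baseline is a response and each arm has its own free baseline mean, the group-by-time term at a visit compares changes from baseline. Randomisation makes the true baseline means equal, and the model does not use that fact. Using baseline as a covariate, or constraining the two baseline means to be equal, estimates the same treatment effect with smaller variance from the same data.

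**Control of the 5% level.** A primary model whose distribution and effects are settled after seeing the outcome has no fixed operating characteristics. The listed indices cannot settle the choice of family either, because QIC belongs to GEE, AIC and BIC belong to likelihood models, and the two are not comparable. If the choice falls on GEE with the usual robust variance, a Wald chi-square reference rejects too often in small samples. How much too often depends on the sample size, which is 104 under Sample size and 40 in the abstract.

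**Working it through.** **Inputs.** From Sample size: VAS means 6.12 to 3.06 (active) and 4.93 to 4.37 (sham), SD 3, power 0.8, alpha 0.05, total 94, and 104 with attrition (52 per arm). From the abstract: 40 (20 per arm). The baseline-to-follow-up correlation ρ is not stated, so a range is used. Two-sided testing is assumed.

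**1. The plan's own figure.** With two arms and two times, the Hotelling-Lawley interaction test is a two-sample t-test on change.

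- Difference in change: (6.12 − 3.06) − (4.93 − 4.37) = 3.06 − 0.56 = 2.50.
- SD of change: 3√(2(1−ρ)), which is 4.243 at ρ = 0.
- Noncentral t: power 0.798 at 46 per arm and 0.807 at 47 per arm, so the total is 94. This reproduces the stated figure.
- At ρ = 0.1, 0.3, 0.5 and 0.7 the total would be 84, 66, 48 and 30. Among the values tried, only ρ = 0 gives 94, and it does so as a pure change contrast.

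**2. Precision against baseline adjustment.** This takes one follow-up visit with equal variance σ² at both times.

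- Change: variance proportional to 2σ²(1−ρ).
- Baseline-adjusted: variance proportional to σ²(1−ρ²).
- Ratio: (1−ρ²)/(2(1−ρ)) = (1+ρ)/2.

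| ρ (assumed) | Variance ratio | Equivalent gain in participants | Total N for 2.50: change / adjusted | Total N for 1.31: change / adjusted |
|---|---|---|---|---|
| 0 | 0.50 | 1/0.50 = 2.00, 100% | 94 / 48 | 332 / 168 |
| 0.3 | 0.65 | 1/0.65 = 1.54, 54% | 66 / 44 | 234 / 152 |
| 0.5 | 0.75 | 1/0.75 = 1.33, 33% | 48 / 36 | 168 / 126 |
| 0.7 | 0.85 | 1/0.85 = 1.18, 18% | 30 / 26 | 102 / 86 |

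The last column is there because the planning means differ at baseline by 6.12 − 4.93 = 1.19 and at the end by 4.37 − 3.06 = 1.31. Randomisation gives no reason to expect that baseline gap, so the adjusted effect may lie anywhere between 1.31 and 2.50.

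**3. Type I error of an uncorrected robust Wald test.** Assume GEE with robust standard errors, complete balanced normal data, n per arm and v = 2n − 2. The robust variance divides the residual cross-products by n² where the unbiased estimate divides by n(n−1). Hence W = T²·n/(n−1), with T² Hotelling on v df, and F = T²(v−p+1)/(pv) on p and v−p+1 df.

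For p = 3 and n = 20: the chi-square cut-off is 7.815; T² = 7.815 × 19/20 = 7.424; F = 7.424 × 36/(3 × 38) = 2.344 on 3 and 36 df; tail probability 0.089.

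| Per arm | Total | 3-df interaction | 1-df contrast |
|---|---|---|---|
| 20 | 40 | 0.089 | 0.064 |
| 47 | 94 | 0.065 | 0.056 |
| 52 | 104 | 0.0635 | 0.055 |

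GEE fitted to simulated null data gave 0.087 (20 per arm) and 0.066 (52 per arm) with complete data, and 0.083 and 0.065 with 10% dropout. Referring the same 3-df contrast to a Hotelling-type F restored about 0.050 at both sizes.

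**The case against.** The strongest reply is that the planned analysis is valid and agrees with its own sample size. Group-by-time is an unbiased comparison in a randomised trial, 94 was computed for exactly that contrast at ρ = 0, and any positive correlation lifts power above plan (0.98 at 47 per arm with ρ = 0.5). This stands: the baseline point concerns efficiency, not validity. It does not remove a gain that costs nothing.

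Some of the remedy is also detail that an analysis plan may hold. That is true of the covariance structure and the degrees-of-freedom method. It is not true of the data-dependent choice of distribution and effects, which the article itself commits to.

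Several stronger readings are tempting, and the document does not support them:

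- *Modelling baseline as a response inflates type I error.* It does not. The inflation comes from an uncorrected robust variance with a chi-square reference, and would arise with or without baseline in the response.
- *The plan's test runs at about 9%.* That needs GEE, robust standard errors, the 3-df test and the abstract's 40. The article does not state robust errors, and 94 (104 with attrition) is the size its Sample size section justifies.
- *Everything is picked from the data.* The article says so for distribution and effects. GEE versus mixed model is left open, not said to be data-driven. Selection by residual plots and fit indices on coded groups is also not selection by p-value or towards an arm, although coding does not rule out a smaller p-value being preferred.
- *Covariates for algometry are chosen after the fact.* The phrase "adjusting for confounders and modifiers effects if necessary" comes shortly after the text on PGI-C and BPI sub-items and may not govern the algometry model. The same ambiguity touches the Wald sentence. The t-tests and chi-square tests are for sociodemographic characteristics, and nothing links them to covariate selection.
- *Partial eta-squared is the only effect size.* The mean difference is planned beside it.

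**Conclusion.** The point holds as two moderate defects.

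1. **Efficiency.** The treatment effect is a difference in change. Baseline adjustment would cut its variance by 35%, 25% or 15% at ρ = 0.3, 0.5 or 0.7. These correlations are assumed, since the article gives none, and the sample-size inputs are for the VAS while algometry is primary.
2. **An unfixed model with uncorrected inference.** Distribution and effects are chosen from the outcome data, the model family is open, and the named test has no small-sample correction. If GEE with robust errors is used, the 3-df test runs at about 6.4% with 104 participants and 8.9% with 40. A 1-df contrast runs at about 5.5% and 6.4%. The excess is modest at 104 and material at 40. No figure is attached to the data-driven choice itself, because the article does not describe it closely enough to compute one.

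A reader might infer from the adjusted sample sizes that fewer participants would do. That does not follow. With the 1.19 baseline gap in the planning means, the adjusted effect may be as small as 1.31, and the adjusted total would then be 168, 152, 126 or 86 at ρ = 0, 0.3, 0.5 or 0.7.

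**What to change.** Replace the open choice with one primary model, fixed before the group codes are broken:

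- Name the single primary algometry measure. Outcomes describes both threshold and tolerance, so the model is not fixed until one is chosen.
- Fit a linear mixed model for repeated measures to the post-baseline values, with visit, group-by-visit and baseline algometry as covariate. Equivalently, keep baseline as a response with its mean constrained equal across arms.
- Use small-sample F or t inference (Satterthwaite or Kenward-Roger). If GEE is preferred, use a small-sample-corrected version.
- Make the adjusted mean difference at the final assessment, with 95% CI, the primary result.
- Move any other distribution or transformation to a named sensitivity analysis. List in advance any further covariates for the primary model, or state that there are none.
- Use the already planned mean difference with CI as the effect measure and drop partial eta-squared. It is a sums-of-squares quantity that neither GEE nor a generalized mixed model produces.
- Leave the sample size alone on this account, and reconcile 40 with 104.

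The cost is wording only. Participant timeline already places the initial assessment before randomisation, so no new data or visits are needed.

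### The form of the PGI-C and BPI analysis is left open, and the contrast the plan targets does not suit PGI-C, whose between-arm comparison is not designated

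*Protocol article*

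**What the plan says.** The Outcomes section of the protocol article names the BPI and PGI-C as secondary outcomes. It scores each of the two BPI dimensions as a mean from 0 to 10. Of the other instrument it says: "The PGI-C will measure change perception". PGI-C runs from 1 (no change) to 7 and refers to change brought about by the intervention.

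The Statistical analysis section then says:
- The main GEE or mixed-model analysis covers "primary and secondary outcomes: algometry, visual analogue scale, EHP-30, Facit-F". BPI and PGI-C are not in this list.
- The model terms are given as follows: "Time, group (active and sham groups), and the interaction between them will represent the independent factors".
- For the two remaining instruments, "the PGI-C and sub-items from the BPI will be analyzed as continuous or dichotomic variables using regression analysis (linear or logistic", with the purpose "to explore the predictors of pain intensity and interference".
- Two sentences later: "We aim to verify the interaction between time and group, adjusting for confounders and modifiers effects if necessary".
- On effect measures: "Effect sizes for interactions will be calculated for all outcomes using the partial η^2^ and mean difference".

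**The concern.** Three features of this text combine badly.

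1. The choice between a mean and a cut, and between linear and logistic regression, is expressly open. No selection rule or cut-off is given, although a continuous BPI score is already defined.
2. The stated purpose is to find predictors of pain intensity and interference. That is a different question from active versus sham, and PGI-C measures neither intensity nor interference.
3. The contrast the plan aims at, and the effect size it promises for every outcome, is the time-by-group interaction. That suits an outcome with a pre-treatment value. PGI-C is already a change rating, so its treatment effect lies in the difference between arms at a visit, not in how that difference varies across visits.

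At stake is how two secondary outcomes are reported: an arm comparison of PGI-C that no one has designated, an interaction effect size near zero beside a possibly real benefit, and room to choose the form of the outcome late.

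**Working it through.** **The plan's own figure.** The only sample-size calculation is for the visual analogue scale; none is given for PGI-C or BPI. Difference in change = (6.12 − 3.06) − (4.93 − 4.37) = 3.06 − 0.56 = 2.50. With SD 3 and zero correlation, the SD of change is 3 × √2 = 4.24. An F test at 0.05 with power 0.80 then needs 47 per arm, total 94 (power 0.807), as stated. This does not bear on the point except to supply sample sizes: 47 per arm evaluable, 52 per arm recruited. The abstract gives 20 per arm, so that is shown too.

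**PGI-C and the interaction.** Assume PGI-C is rated at the three post-treatment assessments only, with a between-arm difference δ at each. The interaction contrasts are differences between visits in the arm difference: δ − δ = 0. The noncentrality is 0, so the rejection probability equals alpha, 5%, at any sample size. A simulation of 20,000 trials per sample size (d = 0.8, between-visit correlation 0.5) gave 4.9%, 5.0% and 5.3% with 20, 47 and 52 per arm.

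**The group term on the same data.** The variance of the arm difference averaged over three visits, in SD units, is (2/n)(1 + 2ρ)/3. For n = 47, ρ = 0.5: (2/47) × (2/3) = 0.0284, SE 0.168. With d = 0.5, z = 0.5/0.168 = 2.97 and power = Φ(2.97 − 1.96) = 84%. Over the assumed range of ρ from 0.3 to 0.7:

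| Per arm | Interaction | Group term, d = 0.5 | Group term, d = 0.8 |
|---|---|---|---|
| 20 | 5% | 42-58% | 81-93% |
| 47 | 5% | 77-91% | over 99% |
| 52 | 5% | 81-94% | over 99% |

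**Other schedules.** With a single PGI-C rating there is no time factor and the interaction cannot be estimated. If a baseline row were coded as no change, the contrast would be δ − 0 = δ and the interaction would respond to a constant benefit. The text does not say this is done.

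**Cost of dichotomising.** One visit, 47 per arm, d = 0.5, normal scores. Continuous: SE = √(2/47) = 0.206, z = 2.42, power = Φ(0.46) = 68%. Dichotomised, by a two-proportion z-test with pooled variance under the null:

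| Cut above sham mean | Sham vs active responders | Power |
|---|---|---|
| 0.25 SD | 40% vs 60% | 48% |
| 1.0 SD | 16% vs 31% | 40% |
| 1.5 SD | 7% vs 16% | 29% |

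**Cost of choosing the form late.** Null simulation, 40,000 trials per sample size, assumed 7-category scale, 20 to 52 per arm. Taking the better of the mean and one cut gives 7.6-7.9% false positives. Taking the best of the mean and three cuts gives 12.3-14.8%. A separate run with the mean and four cuts on a uniform 7-point scale gave 13.6%. The range is about 8-15%, against a nominal 5%.

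**The case against.** A reader might infer that the plan cannot detect a lasting PGI-C benefit and would report a null result. The documents do not support that. Group is a model factor, Wald tests of individual terms are planned, and mean differences with confidence intervals and p-values are to be given at the final assessment and follow-ups. A constant benefit would show in the group term. What stands is narrower: neither that term nor a visit-level difference is designated as the PGI-C comparison, and the promised effect size is for the interaction.

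The sentence stating the interaction aim names no outcome and could be general. It does, however, follow directly on the PGI-C and BPI text, and the effect-size sentence covers all outcomes.

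The PGI-C schedule is in figures that are not shown, so the 5% result is conditional on post-treatment ratings at several visits.

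The interaction criticism does not extend to BPI, which can have a baseline. The BPI also mixes item types (scores, percentage relief, treatments used), so the open form could mean matching the model to the item. That reading does not help PGI-C, a single scale, or the two domain scores.

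A reader might also infer that the form will be picked after results are seen. The text does not say so; it only fails to prevent it. A cut-off is often left to a separate analysis plan, but here the article itself permits either form. Finally, the predictor regressions are already described as exploring, so little needs changing there.

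**Conclusion.** The point holds in limited form. The article leaves the outcome form of two secondary instruments open, ties their regression to a question other than the randomised comparison, and targets a contrast that does not suit PGI-C. The cancellation of a constant PGI-C benefit is algebra and needs no assumption beyond ratings taken only after treatment, at more than one visit. The power and error figures rest on assumed effect sizes, correlations, cuts and category distributions, and the 8-15% applies only if the form is selected after seeing results. Because these are secondary outcomes and a group test would exist in the model, this is a correction that should be made, not a threat to the trial's main conclusion.

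**What to change.** - **BPI:** analyse the two domain scores, as already defined, as continuous outcomes in the same longitudinal model as the other outcomes, with the arm difference in change from baseline as the estimate.
- **PGI-C:** designate the between-arm difference at each post-treatment visit where it is collected (mean difference or proportional odds) as both comparison and effect measure, replacing the interaction for this outcome. State those visits in the text.
- **Responder analysis:** if wanted, make it supportive, with the cut-off fixed before unblinding.
- **Predictor regressions:** keep them separate from the arm comparison and labelled exploratory.

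The cost is a few sentences in the Statistical analysis section. No extra data, visits or participants are needed.
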